## Abstract

**Background:** Rheumatoid arthritis (RA) is a chronic inflammatory disease characterized by autoantibody production and synovial membrane damage. It significantly impairs overall function and quality of life. Consumption of omega-3 (n-3) polyunsaturated fatty acids (PUFAs) and regular aerobic exercise (AEx) training are reported to have positive effects on the progression of RA. However, the mechanisms behind these benefits are still inconclusive. This study protocol will investigate the effects of n-3 PUFA supplementation and AEx training on disease progression, cardiometabolic health, and quality of life, and their association with the plasma and synovial fluid levels of specialized pro-resolving mediators (SPMs) in subjects with RA.

**Methods:** The study consists of a 16-week intervention period, during which participants will be randomly assigned in a double-blinded manner to one of four groups: placebo control (PLA), PLA+AEx, n-3, or n-3+AEx. The PLA groups will be given a gelatin-filled capsule, while the n-3 groups will be given n-3 PUFAs equivalent to 2.5 g/d of docosahexaenoic acid and 0.5 g/d of eicosapentaenoic acid. The AEx groups will perform exercise three times per week on a stationary electronically braked cycle ergometer at 60-70% of their VO2peak for 50-60 minutes. Before and after the intervention, participants will undergo RA-specific and functional measurements, peak aerobic capacity test, and a dietary and physical activity assessment. Venous blood and synovial fluid from the knee joint will be collected. Changes in disease progression, cardiometabolic health, and quality of life, as well as erythrocyte membrane composition to assess n-3 incorporation, SPM levels, inflammatory markers, and gene expression from blood and synovial fluid will be analyzed.

**Conclusions:** The study aims to elucidate the SPMs that regulate the inflammatory gene expression pathways and associate them with the improvements in disease progression, cardiometabolic health, and quality of life after n-3 PUFA supplementation and AEx training.

**Registration**: ClinicalTrials.gov
#NCT05945693.

## Introduction

Rheumatoid arthritis (RA) is an autoimmune and chronic inflammatory disease characterized by autoantibody production [rheumatoid factor (RF) and anti–citrullinated protein antibody] and damage of the synovial membrane of the joints, causing swelling, pain, stiffness, and fatigue, among other symptoms.
^
1
^
^,^
^
2
^ The chronic inflammation around the joints leads to substantial damage to the cartilage, bones, tendons, and ligaments, thereby, significantly impairing overall function and quality of life.
^
3
^ As a result, RA patients have a 50% greater chance of developing cardiometabolic diseases,
^
4
^ such as hypertension, insulin resistance, obesity, and sarcopenia, thereby increasing the propensity of further disability and mortality.
^
1
^
^,^
^
5
^
^–^
^
7
^ Worldwide, RA affects 0.2-1.0% of the total population, with a higher prevalence in women, being 3 to 8 times more frequent than in men.
^
8
^
^,^
^
9
^

Treatments for RA include the prescription of antirheumatic/anti-inflammatory pharmacological and biological medications such as nonsteroidal anti-inflammatory drugs (NSAIDs), corticosteroids, and disease-modifying antirheumatic drugs (DMARDs). They lead to significant improvements in functionality (decreased stiffness) and quality of life; however, they result in increased healthcare costs. Importantly, these treatments have no effect or even augment the cardiometabolic risk factors associated with this disease, probably due to the sedentary lifestyle and poor dietary patterns of RA individuals.
^
5
^
^–^
^
7
^ Furthermore, as these traditional treatments target and inhibit the signaling pathways that produce inflammatory cytokines, including tumor necrosis alpha (TNF-α) and interleukin-6 (IL-6), they lead to immunosuppression and other unwanted side effects.
^
10
^ Interestingly, there is substantial evidence supporting that consumption or supplementation with omega-3 (n-3) polyunsaturated fatty acids (PUFAs) and regular aerobic exercise (AEx) training have positive effects on RA. For instance, several studies report significant benefits of n-3 PUFA on clinical and functional outcomes in RA individuals, usually when high doses were used (> 2g/d).
^
11
^
^–^
^
13
^ In particular, regular consumption of fish oil rich in n-3 PUFAs leads to the incorporation of eicosapentaenoic acid (C20:5n-3, EPA) and docosahexaenoic acid (C22:6n-3, DHA) into blood and synovial fluid phospholipids.
^
14
^ This has been shown to improve several disease-specific and functional outcomes of RA, such as morning stiffness,
^
15
^ joint pain,
^
16
^ number of swollen and tender joints,
^
17
^ grip strength,
^
18
^
^,^
^
19
^ decreased NSAID consumption,
^
15
^
^,^
^
20
^ and health-related quality of life.
^
13
^ In addition, regular consumption of n-3 PUFAs decreases the serum levels of the proinflammatory mediator thromboxane B
_2_ (TXB
_2_) and the production of prostaglandin E
_2_ (PGE
_2_) after 24 h incubation of blood with lipopolysaccharide (LPS).
^
20
^ Moreover, n-3 PUFA supplementation reduces the production of several pro-inflammatory cytokines, including the blood levels of C-reactive protein (CRP),
^
21
^ TNF-α
^
22
^ and IL-1β.
^
18
^ Surprisingly, the specific mechanisms behind the anti-inflammatory and positive health-related effects of n-3 PUFAs in RA individuals are still inconclusive.

The regular practice of physical activity/exercise is also an effective and multifactorial approach for improving several aspects of health in RA subjects, including cardiovascular, metabolic, musculoskeletal, and functional health.
^
23
^ For instance, RA participants who performed 6 months of regular AEx [3 times per week at 70% of peak oxygen consumption (VO
_2_peak)] improved their cardiorespiratory fitness (8% VO
_2_peak) and cardiometabolic health.
^
24
^ Furthermore, AEx training improved symptoms and specific clinical measures of RA, including the perception of fatigue, joint pain, physical function (decreased walk time and increased grip strength), quality of life [health assessment questionnaire HAQ)], and RA disease activity score (23%).
^
6
^
^,^
^
23
^
^–^
^
26
^ These beneficial effects are most likely mediated by the anti-inflammatory effects of exercise; however, the mechanisms behind this effect are not yet known.

Because some of the putative mechanisms behind the effects of n-3 PUFA supplementation and AEx training overlap,
^
27
^
^–^
^
29
^ the combination of these treatments in individuals with RA may further improve their health. However, to date, no study has examined the effects of n-3 PUFA supplementation and AEx training in individuals with RA. Further, the emergence of a novel class of lipid metabolites derived from n-3 PUFAs – specialized pro-resolving mediators (SPMs) – which activate pathways that reduce excessive inflammation, yet also enhance pathways necessary for tissue repair and regeneration,
^
30
^
^,^
^
31
^ has initiated a promising new era of research that could explain the benefits observed after n-3 PUFA supplementation and AEx in individuals with RA. However, whether they are responsible for this adaptive response, also remains to be elucidated.

*Research hypothesis:* N-3 PUFA and AEx will have synergistic effects on disease progression, cardiometabolic health, and quality of life in individuals with RA, and these changes will be associated with SPM production in blood and synovial fluid.

*General aim:* To investigate the effects of n-3 PUFA supplementation and AEx training on disease progression, cardiometabolic health, and quality of life and their association with the plasma and synovial fluid levels of SPMs in individuals with RA.

*Specific aims*:
(1)To compare the effects of n-3 PUFA supplementation, AEx training, and the combination of both on disease progression, cardiometabolic health, and quality of life in individuals with RA.(2)To compare the effects of n-3 PUFA supplementation, AEx, and the combination of both on the plasma and synovial fluid levels of the SPMs in individuals with RA.(3)To examine the relationship between the plasma levels of the n-3 PUFA derived SPMs with systemic disease progression, cardiometabolic health, and quality of life in individuals with RA

To achieve these aims we have designed a randomized, 16-week, placebo-controlled, blinded interventional trial.

## Protocol

### Study settings

Participants will be recruited from hospitals and private clinics in the central region of Chile, whereas all the interventions regarding AEx will be carried out at the Universidad de O’Higgins and the Hospital Regional de Rancagua. All institutions are in the Región del Libertador Bernardo O’Higgins, Chile.

### Sample size

The sample size calculation for this study is based on an α level of 0.05, a power (1-β) of 0.8, and effect size of 0.42 (morning stiffness).
^
11
^ A minimum of 18 participants are necessary per group; however, 22 individuals will be recruited to account for a typical dropout rate of 20% in long-term intervention studies.

### Participants

88 individuals (18-65 y) with rheumatoid arthritis (RA) will be recruited via newspaper advertisements, posters, flyers, visits to local community centers, and referrals from associated centers and Rheumatologists. All participants will obtain medical clearance from their Rheumatologist before taking part in the study. Individuals with moderate disease activity, as defined by the Disease Activity Score 28 (DAS28) > 2.6 and < 5.1 will be included. Participants taking nonsteroidal anti-inflammatory drugs (NSAIDs), glucocorticoids, or disease-modifying anti-rheumatic drugs (DMARDs) will be eligible; however, the dosages of these agents must be constant at least four weeks before, must remain within this limit throughout the study, and prednisone dose should not be higher than 7.5 mg/d.
^
32
^ Individuals diagnosed with gastrointestinal or metabolic diseases, regular alcohol abuse, smokers, and dietary supplement intake (e.g., fish oil capsules) or consumption of fish > 2 times per week will be excluded. Further, individuals that perform regular aerobic exercise (> 150 min moderate intensity per week) or have any physical or biomechanical limitations to complete the exercise program will also be excluded. Finally, subjects will be excluded if they present blood levels of aspartate aminotransferase, alanine transaminase, or creatinine higher than 1.5 times the maximum normal limit and total bilirubin levels of more than 1.8 mg/dL.
^
33
^
^,^
^
34
^ Participants will be encouraged to continue with their everyday normal activities. They will be fully informed of the nature and possible risks of the experimental procedures before providing their written informed consent. Participation in this study is voluntary.

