### Ethical considerations

Due to ethical considerations (divergent inflamed joints between participants), we will only perform the synovial fluid procedure in a small subset of patients from each intervention group. We will ensure that all individuals receive the best medical attention before, during, and after the procedure. Before a participant is eligible, a full medical screening will be performed to assess any risks. The individuals will be followed up routinely 48 h after the procedure to check if any complication occurs, which is unlikely. If a complication occurs, the principal investigator of this study will take care of all associated medical procedure costs and will seek the best treatment for the participant.

This study received ethics approval from the Comité de Ética de Investigación en Seres Humanos #219-2021 (Universidad de Chile, Santiago, Chile). All participants must sign a consent form prior participation in the study.

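### The laboratory exclusion joins its two limits with *and*, so read literally an isolated rise in AST, ALT, creatinine or bilirubin does not exclude a patient

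*Protocol article*

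**What the plan says.** The laboratory criterion appears once, near the end of the eligibility text in the Participants section. It excludes subjects who present with "aspartate aminotransferase, alanine transaminase, or creatinine higher than 1.5 times the maximum normal limit and total bilirubin levels of more than 1.8 mg/dL". It has two parts. The first sets a common limit for three markers, AST, ALT and creatinine. The second adds bilirubin, and the connector between the two is *and*.

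Two general safeguards also bear on entry. The Participants section states "All participants will obtain medical clearance from their Rheumatologist before taking part in the study", and the Ethical considerations section states "Before a participant is eligible, a full medical screening will be performed to assess any risks". Neither gives a laboratory limit.

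**The concern.** Two different connectors stand in one conditional sentence. *Or* links AST, ALT and creatinine; *and* links that group to bilirubin. The ordinary logical reading is that both parts must be true before the patient is excluded. On that reading, a patient whose creatinine is well above the limit but whose bilirubin is normal passes the criterion, as does a patient with raised bilirubin and nothing else.

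This is the only numerical laboratory safety exclusion in the article. Patients on stable NSAIDs, glucocorticoids or DMARDs may enter, and recruitment runs through several hospitals and private clinics (Study settings). The rule should therefore read the same way to everyone who applies it, and a reader of the results should be able to tell who was kept out. This is not a complaint about missing detail: the criterion is stated, with its thresholds, and the defect is in how its parts are joined.

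**Working it through.** The article gives no figure to reproduce. The check is one of logic, followed by a search for text that would decide the reading.

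**Inputs (all from the Participants section).**
- A: AST above 1.5 times the upper normal limit
- B: ALT above 1.5 times the upper normal limit
- C: creatinine above 1.5 times the upper normal limit
- D: total bilirubin above 1.8 mg/dL

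**The two readings.**
- Joint (literal): exclude if (A or B or C) and D.
- List: exclude if A or B or C or D.

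**Count.** Four yes/no conditions give 2^4 = 16 combinations. One has no abnormality, leaving 16 − 1 = 15 with at least one. Among A, B and C there are 2^3 − 1 = 7 combinations with at least one raised.

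| A, B, C | D (bilirubin) | Combinations | Joint reading | List reading |
|---|---|---|---|---|
| At least one raised | Raised | 7 | Excluded | Excluded |
| At least one raised | Not raised | 7 | Not excluded | Excluded |
| None raised | Raised | 1 | Not excluded | Excluded |
| None raised | Not raised | 1 | Not excluded | Not excluded |

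The joint reading excludes 7 and the list reading 7 + 7 + 1 = 15. They disagree on 15 − 7 = 8: the seven with a marker raised and bilirubin within its limit, and the one with bilirubin raised alone.

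**Does other text decide it?**
- An earlier exclusion sentence in the same section uses *and* as a list joiner: "regular alcohol abuse, smokers, and dietary supplement intake (e.g., fish oil capsules) or consumption of fish > 2 times per week will be excluded". Each item there plainly excludes by itself. This favours the list reading.
- The disease-activity criterion uses *and* as a joint condition: "DAS28) > 2.6 and < 5.1 will be included". This is weak evidence, because a lower and an upper bound on one score can only be joined by *and*.
- The limits are not restated elsewhere, and no phrase such as *any of the following* introduces them. The section on clinical, cardiometabolic and inflammatory blood measurements does not name these four markers.
- Clearance and screening carry no laboratory values, so neither tells a screener which reading to apply.

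The evidence leans towards the list reading but does not establish it.

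**The case against.** The strongest reply is that no clinician would apply the joint reading. A creatinine limit that operates only when bilirubin is also high has no evident purpose, and the closest comparison in the same section, the exclusion sentence on smoking and supplements, uses *and* as a plain list joiner. The document is also a journal article: the working eligibility checklist belongs to a full protocol that is not shown, so sites may never meet the ambiguous wording. Clearance by the rheumatologist still applies to every participant, and a medical screening is described as well. Finally, counting combinations gives them all equal weight and says nothing about how many patients would be affected.

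Much of this stands. The list reading is the more likely intention, the disease-activity range is a poor counter-example, and the count describes logic, not patients. The point concerns wording, not a contestable design decision. What does not follow is that the text is sound. The laboratory sentence is built differently from the smoking and supplements sentence: it is a conditional that mixes *or* and *and*, and its literal meaning is the permissive one. A safety criterion should not depend on the reader reversing its literal meaning by inference. The screening sentence stands in the discussion of the synovial fluid procedure and may cover only that subgroup; like the clearance requirement, it contains no threshold that would fill the gap.

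**Conclusion.** The concern holds, as a minor defect of wording in a safety criterion. As printed, the rule can be read in two ways that give opposite results whenever the abnormality lies on one side of the *and* only, which is 8 of the 15 abnormal combinations. The literal reading is the less protective one and is probably unintended.

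The number of patients affected cannot be derived, because the article does not say how often these abnormalities occur in the recruited population. Nothing here shows that anyone has been or will be wrongly enrolled; a patient who passes this criterion must still obtain medical clearance. There is no consequence for sample size, power, the primary outcome or the analysis. The conclusion rests only on the printed sentence and on the absence of any text in the article that fixes its meaning.

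**What to change.** Replace *and* with *or* before the bilirubin limit, so that any one of the following excludes: AST, ALT or creatinine above 1.5 times the upper normal limit, or total bilirubin above 1.8 mg/dL. Setting the four limits out under *any of the following* would do the same. Leave the thresholds as they are. If screening has already taken place, state which reading was applied.

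The cost is one word in the eligibility text, with no additional test.

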### Study design

This study consists of a 16-week intervention with n-3 PUFAs and/or aerobic exercise (AEx) training. The subjects will be randomly assigned in a double-blinded manner to one of four groups: placebo control (PLA), PLA+AEx, n-3, or n-3+AEx. A stratified randomized assignment (by block) process will be employed to ensure that the experimental groups are balanced for disease activity, pharmacological treatment, sex, and age. The principal investigator and pharmacy personal will be aware of patient allocation and will code the information. Patients and exercise intervention supervisors will be blinded for supplement intervention, while medical specialists and database analysis personal will be blinded for supplement treatment and exercise intervention. The study will be unblinded for patients and medical specialist if the participant worsens their condition according to the criteria described below or if they decide to drop out the study.

The training sessions will be conducted at the Laboratorio de Ciencias del Ejercicio en el Ciclo Vital (Lab-CERVITAL), Universidad de O’Higgins. The week before intervention the participants will perform RA specific tests (e.g., Disease Activity Score-28) and functional measurements (e.g., handgrip strength), peak aerobic capacity test, a dietary and physical activity assessment, and blood samples will be collected. Subsequently, participants will start their 16-week intervention (PLA, PLA+AEx, n-3, or n-3+AEx). At the end of the intervention the same initial measurements, questionnaires, and assessments will be collected. In a subgroup of participants (n=24 in total or n=6 per group) extraction of synovial fluid will be performed before and after the intervention.

### Primary and secondary outcomes

Primary outcome: Early morning stiffness is one of the main outcomes significantly improved by n-3 PUFA supplementation in RA patients.
^
11
^ Therefore, the difference in the duration (minutes) of early morning stiffness has been selected as the primary outcome to compare the intervention effect in each group after the intervention period.

Secondary outcomes: Other relevant outcomes which allow the assessment of disease progression will be measured, such as the Disease Activity Score-28, DHA-SPMs, tender and swollen joint count, quality of life, grip strength, analgesic use, and TNF-α blood levels.

### Supplementation and exercise intervention

The participants will be supplemented with either 5 capsules per day of Omega UP (Newscience, Chile) equivalent to 2.5 g/d of DHA and 0.5 g/d of EPA or a placebo filled gelatin capsule. The current doses are within the limits recommended by the European Food Safety Authority and have been shown to be safe, to be incorporated into cell membranes, and to produce significant improvements in overall health in individuals with RA.
^
35
^
^–^
^
38
^ Capsules will be placed into de-identified bottles by people not involved in the study and provided to the participants to ensure double blinding.

Patients will be given 2-4 weeks of capsules at a time, with all capsules counted before and after this timeframe, and a small notepad will be provided for them to write down every time when the capsules are taken. Furthermore, patients will receive weekly phone calls and text messages to serve as reminders for treatment adherence. Capsule treatment will be discontinued if patients worsen their condition or if the patient decides to drop-out without questioning their decision.

The exercise intervention will be performed according to the recommendations from the European Alliance of Associations for Rheumatology (EULAR) consisting of aerobic type exercise training three times per week, on non-consecutive days, with a total time of 20-60 minutes.
^
25
^ The AEx will be performed on a stationary electronically braked cycle ergometer starting at 40-50% of VO
_2_peak for 20 minutes. The intensity and volume of cycling will then be gradually increased to target at least 60-70% of VO
_2_peak for 50-60 minutes over the final 10 weeks. Heart rate, power output and rating of perceived exertion (RPE) will be monitored during training intervention.

A brief talk about the exercise importance for their conditions will be made every first session of the week to create awareness about it. Also, sessions have been planned at moderate intensity to decrease the risk of discomfort and to improve adherence. The exercise intervention will be stopped if the patient presents any discomfort related to fatigue, consciousness, cardiac, respiratory, or muscular hassle. Furthermore, if at some point disease symptoms are an obstacle for exercise practice, the patient will be advised to drop out the study. Finally, all patients in the exercise group may drop out from the study at any point without justification.

In case of any question or inquiry during the follow-up, the patients will be given a phone number and email to contact study the personnel. Furthermore, during the phone calls made by the personnel a question regarding compliance with the study will be asked. If these measures are not enough for promoting participant retention and the patient decides to drop out, a question regarding their reason for discontinuation will be asked. This information will be analyzed to avoid future study dropouts.

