### Statistical analysis

Results will be expressed as mean ± SD. A two-way ANOVA with repeated measures followed by Fisher’s least significant difference post-test for multiple comparisons between groups will be used. Linear regression models will be constructed to examine the association between SPMs and clinical, functional, and health parameters, accounting for participant age, sex, and BMI as covariates. A value of p<0.05 will be considered statistically significant.

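### Advice to leave the study when symptoms obstruct exercise can apply only in the two exercise arms, so exercise versus non-exercise contrasts can be biased toward exercise by an unknown, probably modest, amount

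*Protocol article*

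**What the plan says.** All places are in the protocol article.

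- **Study design.** Patients are randomised to "one of four groups: placebo control (PLA), PLA+AEx, n-3, or n-3+AEx". Measurements are taken in the week before the intervention and repeated at its end. No visit in between is described.
- **Primary and secondary outcomes.** The primary outcome is the difference in duration of morning stiffness, in minutes.
- **Supplementation and exercise intervention.** There are two separate exercise rules. The first stops the treatment: "The exercise intervention will be stopped if the patient presents any discomfort related to fatigue, consciousness, cardiac, respiratory, or muscular hassle". The second concerns the study itself: "if at some point disease symptoms are an obstacle for exercise practice, the patient will be advised to drop out the study".
- **Same section, all four arms.** "Capsule treatment will be discontinued if patients worsen their condition or if the patient decides to drop-out without questioning their decision".
- **Study design, all four arms.** "The study will be unblinded for patients and medical specialist if the participant worsens their condition according to the criteria described below". The same sentence also unblinds when a participant decides to drop out.
- **After drop-out.** The article describes only a question about the reason for leaving.
- **Statistical analysis.** "A two-way ANOVA with repeated measures followed by" Fisher's least significant difference test.

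**The concern.** The second exercise rule ties leaving the study to symptomatic disease, and it can apply only to patients assigned to exercise. A PLA or n-3 patient with the same symptoms has no exercise session for the symptoms to obstruct. The trigger is also close to what the trial measures: stiffness is a disease symptom, and tender joints and the patient's global assessment enter the DAS28.

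If the advice is followed, the exercise arms reach week 16 without some of their more symptomatic patients, while comparable patients in the other arms may still be measured. Missing values then depend on the outcome and differ by arm. The expected direction favours exercise, and any worsening of disease under exercise would be under-recorded. The contrasts at stake are PLA+AEx versus PLA, the combination versus n-3 alone, the combination versus PLA, and the pooled exercise comparison. Specific aim 1 needs these contrasts.

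**Working it through.** **1. The rules side by side**

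| Event | PLA, n-3 | PLA+AEx, n-3+AEx |
|---|---|---|
| Condition worsens | capsules stopped, unblinding | capsules stopped, unblinding |
| Discomfort during exercise | cannot arise | exercise stopped |
| Symptoms obstruct exercise | cannot arise | advised to leave the study |

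Only the last row removes a patient from the study, and only in two arms.

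**2. The plan's own figures**

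The Sample size section gives α 0.05, power 0.8, effect size 0.42, 18 per group, and 22 recruited for 20% dropout.
- With 0.42 read as Cohen's f in a one-way, four-group ANOVA, power is 0.815 at 17 per group and 0.840 at 18, so the stated 18 is reproduced to within one patient.
- With 0.42 read as a standardised mean difference d, 89 per group would be needed.
- For dropout, 18 × 1.2 = 21.6, giving 22; 18 / 0.8 = 22.5 would give 23.
- For two equal groups d = 2f, so f = 0.42 corresponds to d = 0.84.

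**3. Bias in change when there is no true effect**

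Assumptions, none given in the article: the most symptomatic fraction q of exercise patients leaves; there is no symptom-driven loss in the other arms; exit symptoms correlate r16 with week-16 stiffness and r0 with baseline stiffness; values are normal; baseline and week 16 correlate 0.5. The SD of change is then √(2 − 2 × 0.5) = 1 in units of the single-time SD.

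Removing the upper tail lowers the mean at each time by r × k, with k = φ(z)/(1 − q). The artificial improvement in change is (r16 − r0) × k.
- q = 0.10: k = 0.1755/0.90 = 0.195
- q = 0.20: k = 0.2800/0.80 = 0.350

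Type I error is from the noncentral t for 36 v 36 (two arms of 18 on each side), two-sided 5%.

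| r16 | r0 | q = 0.10: bias, type I | q = 0.20: bias, type I |
|---|---|---|---|
| 0.5 | 0.25 | 0.049 SD, 5.5% | 0.087 SD, 6.6% |
| 0.7 | 0.35 | 0.068 SD, 5.9% | 0.122 SD, 8.1% |
| 0.7 | 0.5 | 0.039 SD, 5.3% | 0.070 SD, 6.0% |
| 0.5 | 0 | 0.097 SD, 6.9% | 0.175 SD, 11.3% |
| 0.7 | 0 | 0.136 SD, 8.8% | 0.245 SD, 17.6% |

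The first three rows give about 0.04-0.12 SD and 5-8%. The last two give 0.10-0.25 SD and 7-18%, and require exit symptoms to be unrelated to baseline. Two other pairings mark the edges. With r16 = r0 the bias is zero. With r16 = 0.7, r0 = 0.25 and q = 0.20 it is 0.45 × 0.350 = 0.16 SD, with type I error 10%.

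**4. Which contrasts are exposed**

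Let the same shift b fall on both exercise arms.
- Exercise minus no exercise: biased by b.
- n-3+AEx minus n-3, and n-3+AEx minus PLA: biased by b.
- n-3+AEx minus PLA+AEx: b − b = 0. n-3 minus PLA: 0.
- Interaction, (n-3+AEx − PLA+AEx) − (n-3 − PLA): (b − b) − 0 = 0.

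**The case against.** **The all-arm rules are a partial counterpart.** A worsening PLA or n-3 patient loses the capsules and the blind, and may well leave. That stands as a limit on the asymmetry, so a reader should not infer that such patients simply carry on undisturbed. But neither rule tells anyone to leave, and both also cover the exercise arms, so the extra exit trigger remains.

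**The frequency is unknown.** The rule is advice. The 20% in the Sample size section is dropout for any reason in every arm, and assigning all of it to symptomatic exercise patients is an upper case. This stands.

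**The larger figures use the wrong quantity.** A reader might take 0.10-0.25 SD as the general size, because that is the shift in the raw week-16 mean. The primary outcome is a pre-post difference, and patients with worse symptoms at exit were probably worse at baseline too. This stands. So does the point that the pooled 36 v 36 test is not named in the plan: for two single arms, 18 v 18, the 0.10-0.25 SD shifts give about 6-11%.

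**The article does not refuse a week-16 visit to those who leave, and gives no missing-data rule.** That is correct. Restriction of the repeated-measures ANOVA to patients with both values is an inference, and an unseen analysis plan may say more. With two measurement times, however, no analysis plan can recover week-16 values that were never collected.

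**Conclusion.** The point holds for contrasts between exercise and no exercise. The rule as written can remove symptomatic patients from the exercise arms only, with no described route to their week-16 values, and the expected bias favours exercise. Under the stated assumptions it is about 0.04-0.12 SD, with type I error about 5-8% at 36 v 36. It rises to 0.10-0.25 SD and 7-18% only if exit symptoms are unrelated to baseline, and it vanishes if they relate equally to both times. The true size cannot be derived from the article.

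Two stronger readings are not supported.
- A reader might infer that the synergy hypothesis itself is biased. If selection is equal in both exercise arms, the interaction is not affected, and supplement versus placebo at the same exercise level is largely protected.
- A reader might set the larger shifts against 0.42 directly and obtain 23-58% of the planned effect. That treats 0.42 as d, whereas 18 per group is reproduced only with 0.42 as f. Against d = 0.84 the larger shifts are about 12-29% (0.10/0.84 to 0.245/0.84), and those that allow for baseline about 5-15% (0.039/0.84 to 0.122/0.84).

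**What to change.** - Leave the rules for stopping exercise and capsules unchanged, but state that stopping treatment is not leaving the study.
- Invite every randomised patient who has not withdrawn consent to the week-16 assessment already planned, and analyse each in the randomised group.
- Reconcile this with the unblinding at drop-out under Study design, so that the week-16 assessor stays blind unless unblinding is needed for care. Medical specialists are otherwise blind to both supplement and exercise, and that would be lost for exactly these patients.

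The cost is protocol wording and some week-16 visits by patients off treatment. The effect estimated will be slightly diluted relative to the on-treatment effect.

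Optionally, the stiffness question could be added to contacts already planned ("patients will receive weekly phone calls and text messages") and all post-baseline values analysed in a mixed model. This would help with patients who still miss week 16, but the correction does not depend on it.
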